## Abstract

Background: The protocol described in this paper is part of a research project coordinated between three Spanish universities, where a technology aimed at improving the quality of life of people with cerebral palsy will be developed. Part of the proposed technology will consist of an interface and a series of applications to increase motivation for daily physical activity. The basis of these developments is the measurement of the emotional state of the subjects. Methods: The experimental protocol is designed with two research objectives, on the one hand to identify the emotional state through physiological signals, and on the other to determine whether music can be a motivating factor to promote physical activity. It is specifically designed for subjects with cerebral palsy, taking into account the special characteristics of this population. These are people with whom it is difficult to use questionnaires to have a basis to contrast with the measured physiological signals, so measurements must be taken in carefully chosen daily-life situations. Discussion: We hope our findings show which physiological parameters are the most robust to measure the emotional state and how to design rehabilitation and physical activity promotion routines that are motivating, in addition to being able to avoid risk factors during the performance of these routines. Trial registration: NCT05621057.

## 1. Introduction

Physical activity is recommended at all ages and for both healthy people and people with functional diversity. The World Health Organization recommends it and even places special emphasis on children and adolescents. In the particular case of people with CP, it is of particular importance. It has demonstrated benefits for motor functions, including enhancing gait speed [1], spasticity [2], balance [3] and muscle strength [4]. It is therefore desirable to find procedures that increase motivation and help to improve the times and routines that this population dedicates to exercise. Detecting the emotional state and fatigue that a subject may have is important, although in this type of population the detection of these states is difficult given individuals’ communication difficulties.

The objective of this experimental protocol is to determine the relationship between physiological measurements and emotional state in children and adults with cerebral palsy (CP). Our research goal is to collect objective and robust information (based on biosignals) about the user’s condition to improve the effectiveness of rehabilitation therapies and the promotion of physical activity, and to determine whether music can improve these outcomes. The knowledge of the user’s emotional state is important to conduct the appropriate activities for their rehabilitation.

The experimentation will be conducted with a group of users belonging to the Association of People with Cerebral Palsy of Seville (ASPACE) and the Director Mercedes Sanroma Special Education School of Seville.

The methodology will be applied to groups of users of different ages with different capacities. For this reason, we have designed a flexible methodology that proposes different tasks according to the context. Certain tasks require physical effort, a factor that must be considered given the potential disruption that it may cause in the data collected [5].

Having an emotional characterization of the user based on their physiological measurements will enable us to obtain a real-time evaluation of the user’s emotions while tasks are being performed. Consequently, activity can be improved by adjusting the required parameters for effective computation, leading to better results.

The challenge we propose to address is that people with severe disabilities struggle to disclose and identify emotional states, which eliminates the possibility of utilizing self-assessment tests for comparison with the collected measures. This requires us to rely on their caregivers, or, alternatively/additionally, to implement measures in everyday scenarios or contexts where the emotional state elicited in the individual is understood.

This experimentation is part of a subproject called AAI (Augmentative Affective Interface), which in turn is part of the AIR4DP (Artificial Intelligence and Robotic Assistive Technology devices for Disabled People) coordinated project that is funded by the Ministry of Science, Innovation and Universities (I+D+i Projects 2019— Society Challenges). The main expected result of the AIR4DP project is the implementation of assistive technology that allows incorporating the latest advances in artificial intelligence (AI) to improve the quality of life of people with disabilities. The AAI subproject seeks an improvement in users’ interaction with systems achieved through knowledge of their emotional state based on physiological measurements and imagery. If this knowledge were injected into a robotic platform or a software platform used in rehabilitation therapies, a greater immersion and motivation of the subject in the proposed activities could be achieved.

The structure of the current paper is as follows. First, a review of the state of the art is presented, taking into account current knowledge on the factors involved in the study of emotional state, the target population (people with CP) and the influence of music on the state of mind. Subsequently, in Section 3, the methodology of the proposed experimentation is described. The type of study and the criteria for the inclusion and exclusion of participants are indicated. The instruments used to carry out the measurements to determine the state of the subjects are listed and explained; these instruments include measurement scales and physiological measurements. Section 4 shows that the chosen sample size is adequate and explains the statistical analysis that will be carried out with the collected data. Finally, in Section 5, we conclude by establishing the importance of designing an experimental protocol in accordance with the characteristics of the subjects that allows for the objectives set out in the protocol to be met.

## 2. Review of the State of the Art

In order to review existing relevant research and create a knowledge base to inform our study, we conducted three searches of research (SCOPUS and IEEE Xplore) with the following keywords:Emotion AND detection AND physical AND activity. We used these keywords to explore methodologies that allow the detection of emotional state during physical activities, or the proposal of physical activity according to a specific emotional state.Emotion AND detection AND cerebral AND palsy. With this search, we intended to detect studies related to the determination of emotional state in people with cerebral palsy. The special characteristics of this population mean that the usual methodologies are not fully applicable, so it is of interest to study cases where this type of measurement was made.Emotion AND elicitation AND music. Music provokes emotions in subjects. The qualities of sound, such as frequency, timbre, duration and intensity, influence the induced emotions, hence its use in therapies. Music can be a way of bringing a subject to a desired emotional state to correlate parameters measured in said state, or music can be used as a form of motivation to carry out activities.

In [6], a health assistant system for subjects with depression was proposed. The system has three facets: the first remembers the taking of medications; the second measures the emotional state of the subjects, focusing mainly on electroencephalography (EEG); and the third proposes exercises based on the previous determination of the emotional state. In [7], physiological signals, specifically electrodermal activity (EDA), also called galvanic skin response (GSR), were used to detect the state of relaxation in subjects. In [8], an experiment with 16 participants was carried out to measure stress in real life. A smartwatch measured temperature, pulse, GSR and acceleration data. Contextual weather information was also measured. The incorporation of the environment measurement increased the precision in the detection of the stress state. In addition, these measures were based on responses to stress self-assessment questionnaires. In [9], a system was proposed to motivate and monitor the physical activity of older adults, based on the emotional state for activity proposals. The system relied on a database called AMIGOS [10]. We present the questionnaires used for both users and caregivers to assess their experience using the system: the questionnaire for users is shown in Table 1 and that for caregivers in Table 2.

In [11], a robotic platform was proposed to encourage physical activity in older adults, with their emotional states measured through images. In [12], cognitive fatigue was measured using a mobile application and 18 people participated in the experiment. The measure is based on the responses of the subjects to mobile games, a questionnaire and software-based facial recognition. In [13], different methods for the classification and processing of the EEG signal were evaluated to detect emotional states caused by a game. In [14], to motivate older people to exercise using a walker, a three-dimensional model of human fitness (arousal, pleasure and fatigue) was proposed. This measurement was used for the control of the walker. Wearable devices were used to measure physiological parameters (EEG, ECG, EMG). The results showed that the proposed solution increased the level of motivation to exercise and prevented muscle damage. In [15], a metric called cross-sample entropy was proposed to analyse EEG signal recordings. The results showed that the extracted parameters were useful to distinguish the states of calmness and distress in the subjects. In [16], artificial intelligence (AI) was used together with information from images and physiological signals to improve the quality of life of older people in nursing homes. The analysis of images and physiological signals enabled AI to propose solutions in different contexts. Authors in [17] introduced SST-EmotionNet, a spatial–spectral–temporal-based network for emotion recognition using EEG; its main advantage is the ability to integrate the features of the spaces mentioned above at the same time. Furthermore, the authors developed a mechanism to discriminate patterns and tested them with two different datasets.

There are few works dedicated to the evaluation of emotional states of people with CP. This topic comprises results from the second set of searches carried out to determine the state of the art. In [18], visually evoked potentials using IAPS imaging were used to analyze evoked emotions in children with CP versus typically developing children. The study was supported by questionnaires in the family environment (KIDSCREEN52) and the Self-Assessment Manikin, administered to the participants who were chosen with the appropriate cognitive level needed to complete this test. The test was carried out with 15 children with CP and 14 children with normal development. It was observed that images with affective content induced lower amplitudes in the brain responses of children with CP compared to those with normal development, which seems to indicate a lower ability to detect emotions. These emotion elicitation techniques will not always be valid, and need to be interpreted with the help of the professionals who attend to the subjects.

In [19], a study with Virtual Reality (VR) was carried out with a 10-year-old girl with a GMFCS (Gross Motor Function Classification System) level of III. The participant’s emotions were analyzed based on facial gestures. In [20], a case study of a girl with cerebral palsy causing communication difficulties with the caregiver was presented. Using a PYTHON image recognition application, the researchers were able to detect patterns that informed the caregiver of their status. In [20], a case study was presented in which the emotional state of a subject with CP was communicated using image recognition. This case attempted to solve the severe communication problems between therapist and patient. The researchers reported limitations related to the lighting required to process the image and the fact that the patient’s disability sometimes made it difficult to detect their emotional state.

Finally, we present previous research in which music is used to induce emotions in subjects. These works show that music can arouse different emotions depending on the musical properties of the piece. In [21], emotions were detected while the subject played a racing video game; the EEG signal was chosen and the classifier was developed by taking the signals from a specific database of emotions. The idea was to insert musical segments into the game according to the emotions detected in the player. In [22], an experiment was carried out where 13 bars with major and minor chords were used as stimuli, different self-assessment scales were used to assess the effect of the musical pieces and the ECG (electrocardiogram) signal and respiration were measured. It was observed that the mode significantly influenced the physiological signals. In [23], an experiment was carried out to see how music affects brain activity, with generated music and classical music as stimuli. Generated music was used so that a possible familiarity did not affect the participant’s emotional state. Using generated music ensures that the emotional state is not based on music that the participant knows from the outset. In this study, classical music was used in search of strong affective responses. EEG and FMRI (Functional Magnetic Resonance Imaging) measurements were taken, and it was observed that the musical stimulus affected the asymmetry in the responses of the two cerebral lobes. In addition to physiological measurements, users also had to respond to tests of their emotional state. In [24], the authors intended to elicit astonishment in users; for this, different musical and Virtual Reality (VR) stimuli were combined. The results were obtained through various self-assessment tests. Physiological measurements were not performed. In addition, as the elicitation of amazement also depends on the personality of the subjects, two additional scales were used; the first measures the predisposition to experience positive emotions and the second measures musical preferences. In [25], an experiment was carried out with 12 people in order to determine the relationship between the EEG signal and emotions. The asymmetry in the value of the EEG signal and its relationship with emotions were studied. To elicit emotions, images from the FACS (Facial Action Coding System) were used to elicit them by imitation and these images were accompanied by music. In [26], the objective was to elicit emotions in the subjects; movie clips were used toward this aim. The clips were chosen to elicit emotional states of happiness, sadness, fear and relaxation. To modify the emotion induced by the scene, music and the color of the ambient light were used for two minutes. In [27], a survey of older people was conducted during the time of the pandemic to assess the role of music as an emotional and social resource. The study shows that as an emotional resource, music induced calm and positive feelings, and as a social resource, it made participants feel accompanied and reminded them of past experiences. In [28], an experiment was designed to determine how music can induce emotions; authors correlated emotions and physiological signals, such as EDA, HR acceleration and others, that showed significant changes between pleasant, neutral and unpleasant 2-second musical extracts.

The reason for conducting this state-of-the-art review in just three lines is due to the absence of studies that have developed measurements for assessing the emotional state of these particular groups. Drawing from existing research in other contexts, various relevant aspects have been evaluated, leading to the formulation of a protocol that amalgamates these findings. This protocol aims to facilitate its application in our specific scenario and with the group of users possessing these unique characteristics. It emerges from years of experience working within these centers, which highlighted the necessity of adapting conventional methods for measuring emotional states and seeking everyday measurement scenarios instead of intentionally inducing emotions, as seen in other contexts described in the literature.

## 3. Materials and Methods

### 3.1. Design of the Study

The first part of the study will be descriptive and observational where the choice of those parameters (dependent variables) that adequately characterize the emotional state of the subjects will be sought. The second part of the study will be analytical, where the influence of music on changes in the selected dependent variables will be determined. In this second part, a single case study will be made, type AB, for each subject, where in condition A the rehabilitation exercise is carried out in silence, while in condition B it is accompanied by motivating music.

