#### 3.3.3. Contexts and Measurement Frequencies

Four sessions will be held, each divided into two parts:

Selection of dependent variables: The objective of the initial two sessions is to establish a baseline for physiological variables during activities that elicit both positive and negative emotions, to use this baseline as a reference in Part 2. The goal is to minimize the reliance on the EVEA tests, as participants may not always be able to articulate their emotions. The EVEA test serves as a supporting tool for a potential automatic classifier.

Session 1: Measurement of parameters when the subject is conducting a pleasurable daily-life activity in the center.Session 2: Measurement of parameters when the subject is conducting an uncomfortable daily-life activity in the center.These sessions will be determined by conversation with the caregivers since they are specific to each subject.

Half of the participants will start with session 2 and then do session 1, while the rest will follow the reverse order.

Music’s influence on the dependent variables: The aim of the next two sessions is to determine the music’s influence on the dependent variables while conducting rehabilitation exercises.

Session 3: Measurement of subject parameters during the performance of rehabilitation activities in the center.Session 4: Measurement of subject parameters during rehabilitation activities in the center. This session will be accompanied by music according to the preferences of the subject.

Each participant will select the music to be played in each session according to their musical preference or, failing that, the music will be selected by their caregiver. The rehabilitation activity should be a gentle exercise for the participant, such as pedaling, extending the limbs or any other activity that can be quantified using inertial units. Furthermore, these activities should be determined by the medical/physiotherapist staff according to the capabilities of each volunteer.

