Even though every session has a unique theme, the format of the sessions will remain consistent. The sensors will initially be placed on the participant and a data acquisition test will be performed to ensure that all data are being captured correctly. Data recording will initiate while the user is responding to the EVEA test; this phase will be used as a baseline for the session—note that a minimum of two minutes is required. The following phase will be the main activity, with a 15 min time limit, ending with a final EVEA test with identical specifications to the initial one, which will be used as the final baseline. Both baselines allow for the detection of the measurement differentials in each session, alongside the analysis of the participant’s progression during the activity. Each participant is expected to finish the protocol within two weeks, where the first and second sessions will be scheduled for the first week, and the third and fourth sessions will be set for the second one. Figure 4 shows a diagram of the described protocol.

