### 4.2. Data Analysis

In general, numerical variables will be expressed as mean (M) and standard deviation (SD), including range, minimum and maximum.

For the first part of the study, we will compare the dependent variables obtained between sessions 1 and 2 for each subject using the permutation test of the difference in means between different data windows. Those dependent physiological variables that mark significant differences for most of the subjects will be chosen. Changes in EVEA test responses between sessions 1 and 2 will serve as reinforcement for detecting the level of emotional change.

We will also correlate the results of the EVEA test with the base state questionnaires to determine the existence of some type of dependency between the base level of EVEA and its variation with respect to the base state. This dependence will be explored with the Spearman or Pearson correlation test.

For the second part, first, we will analyze the variation in EVEA for sessions 3 and 4 to determine if there is a significant dependence on the independent variable (music) between stages A and B for all the participants. We will use the Kruskal–Wallis test, which does not require any type of assumption regarding the normality and homoscedasticity of the samples. These variations will also be correlated with the quality of life scale (ICF, GMFCS, MACS, CFCS, or KIDSCREEN), as was carried out with the data from the first part.

For the physiological variables and the average kinetic energy, we will determine if their variations are significant between A and B by means of a Kruskal–Wallis test applied to the group of subjects, but also at the individual level by means of a permutation test.

The significance of the tests will be set at three levels, indicated with * (*p* < 0.05), ** (*p* < 0.01) and *** (*p* < 0.001).

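### Part 2 as written runs one silent session and then one music session with no order reversal, so the A–B difference cannot be attributed to music

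*Protocol article*

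**What the plan says.** Section 3.1 describes Part 2 as the analytical part, in which "a single case study will be made, type AB, for each subject, where in condition A the rehabilitation exercise is carried out in silence". Condition B is the same exercise with motivating music added.

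Section 3.3.3 assigns the conditions to sessions:
- Condition A: "Session 3: Measurement of subject parameters during the performance of rehabilitation activities in the center".
- Condition B is session 4, the same kind of activity: "This session will be accompanied by music according to the preferences of the subject".
- Schedule: sessions 1 and 2 fall in week 1, and "the third and fourth sessions will be set for the second one".
- Order: the only rule is "Half of the participants will start with session 2 and then do session 1, while the rest will follow the reverse order". It names sessions 1 and 2. Nothing comparable is given for sessions 3 and 4, and no return to silence follows the music session.
- Baselines: each session opens and closes with an EVEA phase, and "Both baselines allow for the detection of the measurement differentials in each session".

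Section 4.2 then compares sessions 3 and 4. For EVEA the purpose is "to determine if there is a significant dependence on the independent variable (music) between stages A and B for all the participants". The physiological variables and kinetic energy are compared between A and B by a group Kruskal–Wallis test and by individual permutation tests. No order or period term is mentioned.

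**The concern.** Whether music motivates physical activity is one of the two research objectives in the Abstract, and Part 2 is the only part that addresses it. If everyone exercises in silence first and with music second, the contrast between conditions is also the contrast between the first and second recorded exercise sessions. Practice, familiarity with the exercise, any habituation still under way and fatigue can all change the response during the second session. Such a change would be reported as an effect of music, or would hide a real one if it ran the other way. The plan protects Part 1 against this by reversing the order for half of the participants, but states no such protection for the part that makes the causal claim. An analysis plan cannot repair this once the sessions have been run.

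**Working it through.** **Inputs from the article.** One session per condition (Sections 3.1 and 3.3.3). Planned enrolment is 40, 20 adults and 20 children (Section 3.2). Section 4.1 supports 36. The lowest significance threshold is 0.05 (Section 4.2). Sidedness is not stated, and two-sided is assumed.

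**The plan's own figure.** Cochran's formula gives n0 = 1.96² × 0.25 / 0.15² = 42.68. The correction for a population of 200 gives 42.68 / (1 + 41.68/200) = 35.3, rounded up to 36. The figure reproduces, but it concerns the precision of a proportion and says nothing about the A–B comparison.

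**Can music and order be separated?** Let s be the subject's level, τ the music effect and π the effect of being the second exercise session.
- Silence first: A = s and B = s + τ + π, so B − A = τ + π.
- If everyone follows this order, the music and period columns of the design are identical (rank 2 for 3 parameters). Only the sum τ + π is estimable, whatever the sample size.
- Music first: B = s + τ and A = s + π, so B − A = τ − π.
- With both orders in equal numbers, the average of the two means is [(τ + π) + (τ − π)] / 2 = τ. Two subjects in opposite orders already give full rank (4 of 4).

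**Do the session baselines help?** Subtracting the opening baseline removes a difference in starting level between days. It leaves π where π acts during the activity, as practice and fatigue do.

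**Do the individual permutation tests help?** Permuting data windows between a subject's two sessions can show that the sessions differ. It cannot show why.

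**Illustrative size.** The documents give no order effect, so a range is assumed, in SDs of the within-subject difference, with τ = 0. A two-sided 0.05 paired t-test declares a music effect this often:

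| Order effect (paired SD) | n = 36 | n = 40 |
|---|---|---|
| 0 | 5% | 5% |
| 0.2 | 21% | 23% |
| 0.3 | 42% | 46% |
| 0.5 | 83% | 87% |

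The planned group test is Kruskal–Wallis, which ignores the pairing. Simulated at n = 40 with normal data and an assumed correlation of 0.5 between a subject's two sessions, it declares a music effect in about 18% of trials at an order effect of 0.3 and 61% at 0.5. At zero correlation it is close to the paired figures (about 44% and 87%). At higher correlation the rates fall further.

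**With both orders.** In simulation with τ = 0 and half the subjects in each order, analysed with period adjustment, the bias is about zero and the false-positive rate about 5% for order effects from 0 to 0.5, at n = 36 or 40. The standard error is unchanged: with 20 per sequence it is SD × √(2/20) / 2 = 0.158 SD, the same as SD / √40.

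**The case against.** **The fixed order is inferred, not stated.** This is correct. It rests on the AB label, the session numbering and an order rule limited to sessions 1 and 2. Figure 4, which shows the timeline, could not be read for this review. The inference is still the natural reading, and nothing in the text points the other way.

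**AB is a declared single-case design.** So it is, but each phase here is a single session, there is no return to A, and the results are also tested across the group. Under a common order, any shared period effect becomes bias.

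**The named mechanisms may be weak.** This stands in part. Sessions 3 and 4 are the third and fourth recordings in the same format, so most of the novelty of the sensors may have passed. The exercise is described as gentle and the activity is limited to 15 minutes, so fatigue may be small. Each session has its own baselines. These points bear on how large π is. They do not make it separable from τ, and sessions 1 and 2 are daily-life activities, so session 3 is still the first recorded rehabilitation session.

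**Staff or rater expectation.** A reader might list this among the things that reversing the order would cure. It would not. Music is audible in either order, and EVEA may be completed by caregivers or relatives who know which condition is running. Expectation about music therefore follows music, not order.

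**Carry-over.** This is a real reservation about reversal, because no gap between sessions 3 and 4 is stated. If music shifts a later silent session by λ, the music-first difference is τ − π − λ and the balanced estimate is τ − λ/2. The article does not give carry-over as a reason for a fixed order, and it already reverses the pleasant and uncomfortable sessions, where emotional carry-over is also conceivable.

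**Conclusion.** The concern holds in this form: under the order the article describes, the A–B difference is estimable but cannot be attributed to music, as Section 4.2 does. That conclusion follows from the design alone and needs no assumption about the size of an order effect.

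Two stronger readings are not supported. One is that Part 2 yields nothing on its objective. It does yield a valid contrast between the two sessions; what fails is assigning that contrast to music alone. The other is that the trial has a false-positive rate of 46% or 87%. Those figures assume order effects of 0.3 and 0.5 paired SD, which the documents do not give, and a paired t-test, which is not the planned group test. With no order effect the paired rate is 5%, and the planned test gives lower rates when the two sessions are positively correlated.

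**What to change.** 1. In Sections 3.1 and 3.3.3, randomise half of the adults and half of the children to do the music session first (10 and 10 in each age group at 40 subjects, 9 and 9 at 36).
2. In Section 4.2, analyse the paired music-minus-silence differences with sequence or period in the model, in place of an unpaired group test of A against B.
3. Report individual A-versus-B permutation tests as descriptive, since one session per condition cannot attribute a subject's change to music.
4. State that rater and staff expectation about music remains under either order.
5. If the order cannot be changed, or the sessions have already been run, state in Section 4.2 and in the conclusions that the A–B difference cannot be attributed to music alone.

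Cost: an allocation list, protocol wording and one model term (38 instead of 39 residual degrees of freedom at n = 40). The sessions, visits and sample size stay the same. The downside is possible carry-over from music into a later silent session. The article should state the gap between the two sessions so that this can be judged.
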